## Abstract

**Introduction:**

Running-related injuries (RRIs) are frequent, but no effective injury prevention measures have been identified yet. Therefore, we have set up the INSPIRE trial in 2017, in which the effectiveness of an online injury prevention programme was tested. Although this programme was not effective in reducing the number of RRIs, we gained new insights from this study, which we used to design an enhanced, online multidisciplinary injury prevention programme. The aim of this study is to test the effectiveness of this enhanced injury prevention programme in a group of recreational runners.

**Methods and analysis:**

For this randomised controlled trial, we aim to include 3394 recreational runners aged 18 years or older who register for a running event (distances 10 to 42.2 km). During the preparation for the running event, runners in the intervention group get access to the enhanced online injury prevention programme. This online programme consists of 10 steps, all covering separate items of RRI prevention. Runners in the control group will follow their regular preparation. With three follow-up questionnaires (1 month before, 1 week before and 1 month after the running event), the proportions of self-reported RRIs in the intervention group and the control group are compared.

**Ethics and dissemination:**

An exemption for a comprehensive application has been obtained by the Medical Ethical Committee of the Erasmus MC University Medical Center, Rotterdam, the Netherlands. The results of the study will be disseminated among the running population, published in peer-reviewed international journals and presented on international conferences.

**Trial registration number:**

NL7694

## Introduction

Running is a popular sport. In the Netherlands, it is practiced by over 2 million people (approximately 12.5% of the Dutch population).^1^ Running has many positive effects on both physical and mental health.^2^ However, the injury rates in running are high. In 2018, there were 750 000 running-related injuries (RRIs) in the Netherlands, which makes running one of the top three sports with the most reported injuries.^3^ More than half of these RRIs required medical treatment. Also the number of RRIs per 1000 training hours is high. In 2018, there were 6.3 injuries per 1000 training hours in running compared with 3.4 injuries per 1000 training hours of all sports together.^3^ These numbers emphasise the need for injury prevention in recreational runners.

Risk factors for RRIs were assessed in multiple studies. A large variety of risk factors were identified in the past decades (eg, overweight, previous injuries and a high weekly running distance).^4 5^ This indicates that the cause of RRIs is multifactorial. However, most prevention studies focussed on modifying one single risk factor for RRIs.^6–8^ For example, Bredeweg *et al* performed an randomised controlled trial (RCT) aiming at the risk factor ‘no previous experience with sporting activities with axial loading’ and offered novice runners a preconditioning programme.^9^ No effect on the number of RRIs was found. Also in other RCTs on RRI prevention in which one risk factor for RRIs (eg, increasing training load too fast or performing no warming-up) was targeted, no effect on the number of RRIs was found.^6 8^ We hypothesised that this ineffectiveness may be due to the fact that these studies targeted only one single risk factor for RRIs, while the cause of RRIs seems to be multifactorial. Therefore, we have set up the INSPIRE trial in 2017, a randomised controlled trial in which we tested the effectiveness of a multifactorial online injury prevention programme in 2378 recreational runners.^10^ This programme consisted of information on evidence-based risk factors for RRIs and advices to reduce injury risk. However, with an injury proportion of 37.5% in the intervention group and 36.7% in the control group, this programme was not effective in reducing the number of RRIs (OR 1.08; 95% CI 0.90 to 1.29).^11^

Although the injury prevention programme of the INSPIRE trial was not effective, some interesting and new insights were gained.^11^ For example, it appeared that the multifactorial online prevention programme seemed to have a negative effect on the occurrence of RRIs in runners with no injury history.^11^ Furthermore, the results showed that runners who applied the information from the biomechanics section of the prevention programme to their training seemed to have an increased injury risk compared with those who did not use this information.^11^ We assume this is the result of the advice on stride pattern. These findings indicate that research on RRI prevention should probably specifically aim at runners who had RRIs in the past. Moreover, advices on stride pattern should not be presented through a website, since this seems to have negative impact on injury occurrence. Probably changes to stride pattern should only be made under supervision of a trainer or physiotherapist.^12^ Participants of the INSPIRE trial indicated that ‘not knowing what to do’ was an important barrier for injury prevention and the participants wished to integrate the injury prevention measures into their training sessions.^13^ This indicates that injury prevention advices should be directive and personalised.

Therefore, we designed an enhanced, online multidisciplinary injury prevention programme entitled ‘10 steps 2 outrun injuries’. The primary aim of this study is to test the effectiveness of this injury prevention programme on the number of RRIs in recreational runners.

## Methods

### Study design

The **S**haping up **P**revention for **R**unning **I**njuries in the **N**etherlands using **T**en steps (SPRINT) study is a RCT in recreational runners who are participating in running events in the Netherlands. Half of the participants of the SPRINT study will get access to the prevention programme during the preparation for a running event, while the other half of the participants will follow their regular preparation for the event. The preparations for the SPRINT study started in December 2018 and in August 2019 the first participants are included. The data collection is finalised in May 2020 and the first results are expected by the end of 2020. The flowchart of the design is shown in figure 1.

### Participants

Potential participants are runners who register for the following running events; DSW Bruggenloop Rotterdam 2019 (15 km), Nacht van Groningen 2020 (10, 16.1 and 21.1 km), NN CPC Loop The Hague 2020 (10 and 21.1 km) and NN Marathon Rotterdam 2020 (10.55 and 42.195 km). On the online registration forms of these running events a question is included, in which the runners are asked whether they are interested in participating in a research project on the prevention of RRIs. Contact information of interested runners is send to the researchers, who will subsequently send more information about the study to these runners. Runners who are still interested in participation are asked to provide electronic informed consent and can immediately fill out the baseline questionnaire.

Only runners aged 18 years or older who register for one of the aforementioned five running events can participate in the SPRINT study. Exclusion criteria include participation in our previous trial on RRI prevention (INSPIRE trial), registration for the running event less than 2 months before the event, no access to internet and/or email and no proper knowledge of the Dutch language. For runners who register for multiple running events, only the first registration is taken into account.

### Randomisation

After completing the baseline questionnaire, the participants are randomised into either the intervention group or the control group. The randomisation is performed in Microsoft Access with a block size of 40. The randomisation table is generated by an individual from outside the research group and this table is not accessible for the researchers during the inclusion and data collection. Both the participants and the researchers are not blinded for the results of the randomisation.

### ‘10 steps 2 outrun injuries’ prevention programme

Participants in the intervention group will get access to the online ’10 steps 2 outrun injuries’ prevention programme. This prevention programme was developed by experts in the field, including human movement scientists, sport physicians, the medical committee of the Dutch Athletics Federation and a sport physiotherapist, based on literature, the expertise of the clinicians and researchers and the results and expertise of our previous trial.^10 11^ The developed ’10 steps 2 outrun injuries’ programme includes 10 steps that all deal with one item related to RRI prevention. Because the aim was to develop a directive and personalised prevention programme, the advices in the programme can be easily applied to running practice and most advices are adaptable to the personal situation of the runners. During the development process, the content and lay-out were discussed with a panel of five recreational runners and their input was taken into account during the development of the RRI prevention programme. In accordance with the preferences of recreational runners, the prevention programme is available on a website and mobile application.^13^ To increase the attractiveness and usability of the prevention programme, the use of text is minimalised and the advices are explained by means of infographics, videos and animations.

All participants randomised to the intervention group will receive a personal login code (username and password) by email. These codes are also used to register the frequency of use of the prevention programme (including the use of the specific elements) of the participants.

#### Step 1: do not change anything if you have no experience with running injuries

A previous injury is the most important risk factor for a new RRI.^4 14^ Furthermore, the results of the INSPIRE trial showed that the prevention programme seemed to have a negative impact in runners who did not suffer an RRI before.^11^ Therefore, runners without previous RRIs are advised not to change anything in their running behaviour. This is a general advice, that is not further specified to specific parts of running behaviour. Furthermore, all steps of the prevention programme are visible to runners without a history of RRIs. This is to enable them to start using the programme if they do experience pain during running in the future.

#### Step 2: do not train too much

Several studies identified associations between training and RRIs. For example, a weekly training distance of more than 30 km was associated with an increased injury risk.^15^ Recently, Nielsen *et al* showed that a weekly increase in training distance of more than 30% is associated with an increased injury risk.^16^ Moreover, it is known from team sports that especially large, sudden changes in training load increase the injury risk.^17–19^ This was confirmed in one study with endurance athletes (runners, triathletes, swimmers, cyclists and rowers) in which an association between high spikes in training load and injuries was identified.^20^ Therefore, runners are advised to use a tool in which they can register and monitor their weekly training load using the acute:chronic workload ratio (ACWR, using the exponentially weighted moving average), which is used to advise runners on the progression in their training schedule.^21 22^ If the ACWR is larger than 1.5, runners are advised to increase their training volume more gradually. For runners who regularly apply interval training, an arbitrary unit (training time multiplied by the rate of perceived exertion) is used to calculate the ACWR.

#### Step 3: make sure there is variety in movement using specific exercises

Strength training has a positive effect on running performance, specifically on the energy costs of locomotion and running economy.^23 24^ Furthermore, strength training is known to decrease the risk of both acute and overuse sport injuries.^25^ Therefore, a training schedule with running-specific exercises is included in the injury prevention programme. This schedule includes three phases of 4 weeks, that all consist of seven exercises. Every exercise is explained in an instruction video which gives a detailed example on how the exercises should be performed. The training schedule is developed by an experienced sports physiotherapist by means of a literature search and his expertise, and was advised to be performed twice a week on non-running days. Considering practicality for the study population and adherence, body weight exercises were chosen. Examples of included exercises are squats, pelvic bridge, tripling and aeroplane pose. These exercises aim to improve neuromuscular control and focus on lower extremity strength and speed, in combination with proper lumbo-pelvic control and stiffness.^26 27^ The exercises are strongly running related, to ensure transfer to running. Progression to more explosive and plyometric exercises at the later stages in the training schedule reflect the literature on this topic.^23 24^

#### Step 4: take enough time for rest and recovery

Generally, injuries are assumed to be the result of an imbalance between training load and recovery.^28–30^ This is shown by the fact that running all year around and participating in more than six running events a year are associated with an increased injury risk.^14 31^ Therefore, step 4 of the prevention programme contains advices on balancing physical activity and rest. To provide clear guidance, the prevention programme includes a recovery scale from 0 to 10 (0 points means no recovery and 10 points means maximum recovery). Runners are instructed to rate physical recovery from their previous running session and other activities before they start a new training session. When the recovery score is higher than 6, runners are advised to continue their training. If the recovery score is between 3 and 6, runners are advised to reduce the distance and intensity of the next training session. When the recovery score is below 3, they are advised to skip the next training session. Furthermore, this step contains the advice to have a break from running of 2 to 4 weeks twice a year. The runners are also advised to slowly build up running again after a break, possibly using the ACWR tool of step 2.

#### Step 5: participate in other sports

Already in 1986, Jacobs showed that runners who did not participate in other sports were more likely to get an RRI compared with runners that did participate in other types of sports.^32^ Buist *et al* later found that previous participation in sports without axial loading was associated with a two times higher injury risk, compared with a history of sports with axial loading.^33^ Based on the studies and the expertise and experience of the clinicians involved in the design of the prevention programme, runners are advised to participate in another sport than running at least once a week. This advice is explained with an animation video.

#### Step 6: do not ignore pain during and after running

The majority of the RRIs are overuse injuries.^34^ These injuries usually start as an uncomfortable feeling or mild pain during running, that increases in severity over time. When runners experience these first signs of an RRI, it is probably wise to adapt training activity accordingly or temporarily stop running. Therefore, the prevention programme includes a 0 to 10 NRS pain scale (0 points means no pain and 10 points means maximum pain imaginable) that guides runners in continuing, skipping or altering the next training session.^35^ After a training session, runners should score the amount of pain during and directly after running. In case of a pain score above 5, the runners are recommended to skip the next training session. When the pain score is between 2 and 5, the advice is to alter the intensity and distance of the next training session. A score lower than 2 results in the advice to continue running.

#### Step 7: wear shoes that feel comfortable

Many runners believe that running shoes play an important role in the occurrence of RRIs.^13 36^ However, so far it has never been shown that RRIs can be prevented by wearing a certain type of shoes or by matching the shoe to the foot morphology.^37–39^ Therefore, runners are made aware of this and are advised to wear shoes that feel comfortable. This information is provided by an interview with an expert sports physician.

#### Step 8: run with a high step rate

A high step rate does not only improve the performance of runners,^40^ but was also associated with a lower likelihood of shin injuries.^41^ In addition, several studies suggest that increased step rate and consequently a decreased step length, does alter running kinematics that have been associated with injuries.^42^ Therefore, the general recommendation to run with a relatively short stride length and high cadence is given to the runners. This is supported with an animation video showing the effects of changing stride length and cadence. Links to digital applications that can be used as guidance to increase cadence are provided.

#### Step 9: plan a gradual increase in race distance within the first years of running experience

Novice runners are known to have a higher chance to develop RRIs than more experienced runners.^43 44^ Novice runners show greater changes in kinematics with fatigue compared with competitive runners, which can make them prone to an RRI.^45^ This implies that novice runners should focus on completing lower running distances before moving on to half marathon and full marathon distances. In the prevention programme, runners are advised to focus on a maximum running race distance of 5 km during the first year of running and gradually increase running distance over the years.

#### Step 10: run with joy

### Sample size

Based on our previously conducted RCT, an injury incidence of 38% is expected in recreational runners participating in running events (10 km up to 42.195 km).^11^ The sample size calculation is based on the subgroup analysis on runners with previous injuries. With a risk difference of 5%, a significance level of 0.05 (two-sided testing and a power of 80%), a minimum of 1414 runners with a previous injury in the previous 12 months should be included in the analyses. The sample size is doubled in order to obtain enough power for the primary analyses in the entire study population. Taking a loss to follow-up of 20% into account, a total of 3394 runners (1697 in each group) should be included.

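### The 1414 previously injured runners do not give 80% power at 38% versus 33% (about 50% as a total, about 79% per arm), and the 38% is an all-runner rate

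*Protocol article*

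**What the plan says.** The Sample size section gives a single event rate: "Based on our previously conducted RCT, an injury incidence of 38% is expected in recreational runners participating in running events". Its source is the previous trial, which the Introduction reports for all of its 2378 recreational runners, "with an injury proportion of 37.5% in the intervention group and 36.7% in the control group". The section then names the group being sized: "The sample size calculation is based on the subgroup analysis on runners with previous injuries". With a 5% risk difference, two-sided 0.05 and 80% power, the result is "a minimum of 1414 runners with a previous injury in the previous 12 months should be included in the analyses". That number is doubled to serve the primary analysis in all runners. After an allowance of 20% for loss to follow-up the target is 3394, or 1697 per group. No injury rate for runners with a previous injury is given.

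Under Step 1 of the programme the protocol says of such runners: "A previous injury is the most important risk factor for a new RRI".

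**The concern.** Two things do not fit.

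First, 1414 is worded as the whole number of previously injured runners needed in the analysis. A 5-point difference from 38% with 80% power needs about twice that.

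Second, the rate comes from all runners but is used for a group that the protocol itself regards as being at higher risk. An overall rate is a weighted average of the previously injured and the rest. If previous injury raises risk, the subgroup lies above the overall rate and the others below it. The same 38% is then unlikely to fit both the subgroup and, after doubling, the whole population.

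At stake is the power claimed for the group at which the programme is aimed (Discussion) and on which the sample size is said to rest. If the subgroup result is null, readers will judge it against a stated 80% that the number may not support.

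**Working it through.** **Inputs.** From Sample size: control rate p1 = 0.38, difference 0.05, two-sided alpha 0.05, power 80%, subgroup number 1414, doubling, 20% loss, total 3394. A reduction is assumed, so p2 = 0.33. Allocation is equal (1697 per group).

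**Step 1: the plan's own figure.** The unpooled formula per arm is

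n = (1.960 + 0.842)² × [p1(1 − p1) + p2(1 − p2)] / (p1 − p2)²

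= 7.849 × (0.2356 + 0.2211) / 0.0025 = 1434 per arm, 2868 in total.

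The pooled-variance version gives 1437 per arm, 2874 in total. A continuity correction raises this to 1477 per arm, and a one-sided test would need 1132 per arm. None of these gives 1414 as a total. As a per-arm number, 1414 is 1.4% to 1.6% below 1434 to 1437.

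**Step 2: power that 1414 gives at 38% versus 33%.** Power = Φ(0.05 × √n / √0.4567 − 1.960), with √0.4567 = 0.6758.

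- 1414 in total, n = 707 per arm: 0.05 × 26.59 / 0.6758 = 1.967, so Φ(0.007) = 50% (pooled 50.2%).
- 1414 per arm: 0.05 × 37.60 / 0.6758 = 2.782, so Φ(0.822) = 79.5% (pooled 79.4%).

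**Step 3: a higher rate in the subgroup.** The documents give no such rate, so 40% to 50% is an assumption used to show a range. The 5-point difference is kept, as the plan states it. Pooled formula:

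| Control rate | n per arm | Change from 1437 | Power, 1414 per arm | Power, 1414 in total |
|---|---|---|---|---|
| 38% | 1437 | – | 79.4% | 50.2% |
| 40% | 1471 | +2.4% | 78.4% | 49.3% |
| 45% | 1534 | +6.8% | 76.7% | 47.7% |
| 50% | 1565 | +8.9% | 75.9% | 46.9% |

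The requirement peaks at 1569 (+9.2%) at a control rate of 52.5% and then declines.

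**Step 4: the same rates with the relative effect held.** If the target is the ratio 33/38, the need falls to 1326 per arm at 40%, 1090 at 45% and 902 at 50%. Power with 1414 per arm rises to 82.5%, 89.1% and 93.9%.

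**Step 5: from 1414 to 3394.** 1414 × 2 = 2828, and 2828 × 1.2 = 3394. A 20% loss from 3394 leaves 3394 × 0.8 = 2715, about 1357 per arm, whereas 2828 analysable runners would need 2828 / 0.8 = 3535. For the all-runner comparison at 38% versus 33%, 1357 per arm gives Φ(0.05 × 36.84 / 0.6758 − 1.960) = Φ(0.766), about 78%. The subgroup's power depends on how many of the 2715 had a previous injury, which the protocol does not state. If it were half, about 679 per arm, power would be Φ(0.05 × 26.06 / 0.6758 − 1.960) = Φ(−0.032), about 49%.

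**The case against.** The base rate is a small matter. Moving it from 38% to 50% costs about 3.5 points of power, which is within ordinary planning uncertainty, and at 40% the cost is about one point. This stands: most of the shortfall is already present at 38%. A reader might infer that the all-runner rate is why 1414 and 80% disagree. Steps 1 and 2 show that it is not.

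The direction is also conditional. A higher rate raises the requirement only because the target is an absolute difference; step 4 shows the reverse for a relative one. The plan does state a risk difference, so the absolute reading is the one to judge it by, but the condition has to be said.

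The Step 1 text gives a direction and no size. It contrasts runners with and without any earlier injury, whereas the sample size subgroup is injury in the previous 12 months, so runners outside the subgroup may include some injured longer ago. A higher subgroup rate is probable rather than shown. Subgroup rates well above 50% can be produced by assuming a prevalence and a risk ratio, but the documents supply neither.

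Finally, the primary outcome is the comparison in all runners, and injury proportion in previously injured runners is secondary. An all-runner rate is the right kind of input for the primary analysis, so the base-rate point does not touch it.

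**Conclusion.** The stated number does not follow from its stated inputs. At 38% versus 33%, 80% power needs about 1434 to 1437 previously injured runners per arm, about 2870 in total. As worded, 1414 gives about 50%; as a per-arm number it gives about 79%. This part rests only on the protocol's own figures and standard formulas.

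The all-runner rate is a further, minor weakness. Under an assumed subgroup rate of 40% to 50% and a fixed 5-point difference, the requirement rises about 2% to 9%. Power is then about 76% to 78.5% with 1414 per arm, or 47% to 49% with 1414 in total. The true excess is unknown.

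A reader might also infer that a rate other than the printed 38% was used, since 37% versus 32% gives 1415 per arm (unpooled). The documents do not support that: 36.7% versus 31.7% gives 1409 to 1412 and fits about as well, and any such match presumes that 1414 is per arm, against its wording. All that can be said is that 38% versus 33% does not yield 1414.

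**What to change.** Rewrite the sample size paragraph in four respects.

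1. Give the control-group injury proportion among runners injured in the previous 12 months, tabulated from the previous trial's data, and use it for the subgroup calculation.
2. Keep the all-runner rate for the primary analysis, and state the rate used in each calculation.
3. Label every number as per arm or total. Correcting the rate without this would leave the subgroup figure wrong by a factor of about two.
4. Restate the power that the planned 3394 gives after 20% loss, separately for previously injured runners (with the expected share of such runners) and for the whole population. Say that the target is an absolute 5-point difference, if that is intended.

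The cost is one tabulation and a reworded paragraph. Enrolment need not change. The price is a less favourable stated power, above all for the subgroup.

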## Discussion

Injuries are a major problem among runners, for which no effective prevention measures have been identified so far. Therefore, the aim of this RCT is to examine the effectiveness of an online injury prevention programme. This programme is aimed at runners who previously suffered from RRIs and includes 10 steps that all deal with one component of running injury prevention. The programme is tested in a large group of runners. Therefore, subgroup analyses based on previous injuries, sex, running experience, distance of running event registered for and injury locations will be possible. Because the programme is presented on a website and mobile application, the programme has the ability to be easily implemented and applied to large and diverse groups of runners if it proves to be effective.

A potential limitation of this study is the use of self-reported RRIs. Runners who are performing with pain may give diverse responses regarding the presence of an RRI. This is partly solved by including the OSTRC Overuse Injury Questionnaire in the follow-up questionnaires, which gives more insight in the severity of the reported RRIs. However, also this questionnaire is patient-reported and subject to the interpretation of the runners. Another possible limitation is that some of the advices in the prevention programme may be subject to the interpretation or motivation of the runners. A runner may, for example, adjust the score on the Numerical

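### The Sample size section claims 80% power from at least 1414 previously injured runners, but the design does not secure that number, and 1414 in total would give only about 50% power

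*Protocol article*

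**What the plan says.** The Sample size section states that "The sample size calculation is based on the subgroup analysis on runners with previous injuries". Its inputs are a 38% injury proportion, a risk difference of 5%, a two-sided 5% significance level and 80% power. From these it concludes that "a minimum of 1414 runners with a previous injury in the previous 12 months should be included in the analyses". That number is doubled, with power for the primary analysis in everyone as the stated reason, and then raised for 20% loss to follow-up to 3394, or 1697 per group.

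The 38% comes from the sponsor's earlier trial and describes event runners in general: "an injury incidence of 38% is expected in recreational runners participating in running events". Step 1 of the programme says of injury history: "A previous injury is the most important risk factor for a new RRI".

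Entry does not depend on injury history: "Only runners aged 18 years or older who register for one of the aforementioned five running events can participate in the SPRINT study". The exclusion criteria in the Participants section do not mention it either, and the Randomisation section describes blocks of 40 without stratification by it. Injury in the previous 12 months is a baseline questionnaire item (Table 1).

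Under Outcome measures, the primary outcome is the between-group difference in injury proportion among all participants. The injury proportion in previously injured runners is a secondary outcome.

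**The concern.** The section makes a promise about one group (a minimum count with 80% power), while recruitment is governed only by a total for a wider group. The two agree only if a sufficient share of participants has a recent injury, and the article gives no such share. The count also looks too small for its own inputs if it covers both arms.

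This is not an incidental subgroup. The Discussion says: "This programme is aimed at runners who previously suffered from RRIs". Step 1 advises runners without earlier injuries to leave their running behaviour unchanged, so any benefit is expected mainly in the previously injured. If their analysis is reported as one the trial was powered for, a non-significant result will be taken as stronger evidence of no effect than it is.

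**Working it through.** **Inputs (Sample size section).** Control proportion p1 = 0.38. The risk difference is read as 5 percentage points in favour of the programme, so p2 = 0.33. Two-sided alpha is 0.05 (z = 1.960), power is 80% (z = 0.842), and allocation is 1:1.

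**1. The route from 1414 to 3394.** 2 × 1414 = 2828, and 2828 × 1.2 = 3393.6, rounded up to 3394. The plan's total is reproduced. However, a 20% loss calls for division by 0.8: 2828 / 0.8 = 3535. With 3394 enrolled and 20% lost, 3394 × 0.8 = 2715 are analysed, not 2828.

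**2. The 1414 itself.** Per-arm size for two proportions, with mean p = 0.355:

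n = [1.960 × √(2p(1 − p)) + 0.842 × √(p1(1 − p1) + p2(1 − p2))]² / (p1 − p2)²

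= [1.960 × √0.45795 + 0.842 × √0.4567]² / 0.05²

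= (1.3263 + 0.5688)² / 0.0025 = 1436.6, so 1437 per arm and 2874 in total.

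Other versions give 1434 (unpooled), 1436 (arcsine) and 1477 (continuity-corrected) per arm; one-sided testing gives 1132 per arm. None gives 1414 for both arms together. As a per-arm figure, 1414 is 1.6% below 1437. With the earlier trial's control proportion of 36.7% (Introduction) and the same 5 points, the formula gives 1412 per arm.

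**3. Power if 1414 is the total (707 per arm).** Power = Φ[(0.05 × √707 − 1.3263) / √0.4567] = Φ[(1.3295 − 1.3263) / 0.6758] = 0.50. With 1414 per arm it would be 0.79.

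**4. Share needed to reach 1414.** 1414 / 2715 = 52.1%. By the plan's own × 1.2 arithmetic (3394 / 1.2 = 2828) it is 50.0%.

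**5. Subgroup size and power with 2715 analysed.** The article gives no share, so the shares below are assumptions. The subgroup is taken to split evenly between arms and to lose 20% like the rest.

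| Assumed share with injury in previous 12 months | Analysed in subgroup | Against 1414 | Power, 38% vs 33% |
|---|---|---|---|
| 30% | 815 | −42% | 0.32 |
| 40% | 1086 | −23% | 0.41 |
| 45% | 1222 | −14% | 0.45 |
| 50% | 1358 | −4% | 0.49 |
| 55% | 1493 | +6% | 0.52 |
| 60% | 1629 | +15% | 0.56 |

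**6. Ceiling.** Even if all 2715 analysed runners were previously injured, power = Φ[(0.05 × √1357.6 − 1.3263) / 0.6758] = Φ[(1.8423 − 1.3263) / 0.6758] = 0.78. The same 0.78 is the power of the whole-population primary comparison at 38% versus 33%.

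**7. The 38%.** If previously injured runners have a higher rate, the same 5-point difference needs more of them. As an illustration with an assumed 45% versus 40%, the formula in step 2 gives 1533.3, so 1534 per arm.

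**The case against.** The best defence is that the sentence is only loosely worded. If 1414 is per arm, doubling is the ordinary step from one arm to two, and 2828 analysed runners give about 79% power for the whole-population comparison whatever the injury mix. That comparison is the primary one, and the mix does not change its sample size. This is probably the most natural account of the arithmetic, and it stands as far as it goes. But it does not rescue the text, which calls 1414 the minimum number of recently injured runners and says the calculation rests on them.

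It can also be said that the sponsor may know the share from its earlier trial of 2378 runners, and that a condensed article need not describe recruitment monitoring. That is fair. A reader might infer that the subgroup will fall far short, or that recruitment stops at 3394 whatever the mix. The article supports neither: it gives no share, and it does not say when recruitment stops. The lower rows of the table are illustrations, not forecasts. The gap between shares of 50% and 52% is minor in itself, since it moves power only from 0.50 to 0.49.

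A reader might further infer that places should be reserved for previously injured runners. The case against that is sound. Event dates are fixed and registration must be at least two months ahead, so turning away other volunteers could reduce the total for the primary analysis. A quota would also change the population studied. And a quota of 1414 would protect a number that yields about 50% power.

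**Conclusion.** The point holds as an error in what the Sample size section claims. The stated minimum is not secured by the entry criteria or the total: it needs a 52% share at 20% loss, and no share is given. More seriously, 1414 does not follow from the stated inputs as a total. In that role it gives about 50% power instead of 80%, and 80% would need about 2874 analysed previously injured runners, more than the 2715 expected in the whole trial. This second part does not depend on any assumed share. It rests on reading the 5% as an absolute difference from 38% and on the stated 20% loss.

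The 38% is an all-runner figure used for a group that the article treats as being at higher risk. The direction of that mismatch is clear, but its size cannot be judged because no rate for the subgroup is given.

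It would go too far to conclude that the primary analysis is seriously underpowered. At about 78% it falls slightly short of 80%.

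**What to change.** Keep the total of 3394 and set no quota. Rewrite the Sample size section so that it:

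- says whether 1414 is per arm or in total;
- gives the share of runners with an injury in the previous 12 months, and their injury rate, as expected from the earlier trial;
- replaces the stated minimum with the number of previously injured runners expected in the analysis from that share, allowing for loss as 3394 × 0.8 × share;
- states the resulting subgroup power, which for 38% versus 33% is about 41% at an assumed 40% share and 49% at 50%, recomputed with the subgroup's own rate once that is given;
- attaches the power claim to the whole-population primary comparison (about 78% with 2715 analysed) and describes the analysis in previously injured runners as having lower power.

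The cost is one rewritten paragraph and two figures from the sponsor's own earlier data. Enrolment, randomisation and the analyses do not change. The downside is that the stated power for the group the programme is aimed at becomes visibly less favourable.
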